#### Data management, data storage, and dissemination policy

In order to protect the confidentiality of participants, their data will be pseudonymize. In accordance to the Good Clinical Practice guidelines, important trial data will be archived for 10 years after the trial’s completion or termination [41]. Patient documents will be stored in compliance with hospital regulations, and access to stored data during and after the trial will be restricted to authorized staff only.

Once the major results of the trial are published, the collected data will be made available in an anonymous format upon reasonable request. Additionally, we will store and provide access to the statistical analysis plan and other relevant documents upon request. Access to the data storage will be limited to authorized personnel exclusively. Patient consent forms will include a section addressing the aforementioned aspects of data storage and sharing.

To disseminate the progress and outcomes of the trial, we have devised several measures. Firstly, we will establish a project homepage that will offer regular updates to the public on the trial’s development, opportunities for participation such as workshops and conferences, and significant findings. This website will remain active even after recruitment is closed, serving as a central hub for future research and dissemination of results. The main trial results will be published in an open-access, peer-reviewed journal and made publicly available through the clinical trial registry. Furthermore, we will present the findings at conferences and communicate scientific results in plain language through press releases, social media, and patient forums. To ensure the results reach the affected population and the general public, we will collaborate with patient representatives and organizations to develop targeted, patient-oriented information campaigns.

#### Statistical methods

The primary objective of this trial is to evaluate the efficacy of the intervention in terms of reducing depression symptoms after the intervention, compared to the control group. To achieve this, we will employ an analysis of covariance (ANCOVA) with the outcome measured at T1, using the between-subject factor of the group (intervention vs. control) and the participants’ baseline values (T0) as a covariate. The primary analysis will be conducted on the intention-to-treat population, with missing data imputed in cases of dropout. Imputation will be performed using the SPSS multiple imputation module, employing “monotone missing pattern” and incorporating complete data for sex, age, and baseline measurements of primary and secondary outcomes. The imputation process will be executed with 3000 imputations, using the analysis date as the seed. Interim analyses are not planned.

Subsequent mixed ANOVAs will be conducted with a between-subject factor representing group membership (intervention vs. control) and a within-subject factor corresponding to the respective measurement points (T0–T3). These analyses will assess whether the effects of the intervention are sustained during the follow-up period. Similar approaches will be applied for the analysis of additional clinical endpoints. In the event of substantial deviations from normality or homoscedasticity assumptions, non-parametric tests, robust procedures such as robust regression analyses, generalized estimating equations, or robust mixed linear models will be employed instead. Corrections, such as Huynh-Feldt or Greenhouse-Geisser, will be implemented if the assumption of sphericity is violated in the mixed ANOVA.

Descriptive analyses will be conducted to assess treatment satisfaction, usability, and usage behavior. For comparisons of demographic and baseline parameters between the two groups, *t*-tests (or Mann-Whitney *U*-tests in the case of non-normality) and *χ*
^2^ tests (or Fisher’s exact tests for variables with small cell sizes) will be utilized. Further mixed ANOVAs will be used to assess the impact of the intervention on the secondary outcome measures, such as eating behaviors (see Table 1). Also here, we will resort to more robust models in case of a violation of assumptions. Also, in case of a significant effect of our intervention on the primary outcome, we will assess whether this result is mediated by increases or decreases in scores concerning eating behavior. Here, we will use mediation analyses on mixed linear models or robust alternatives (such as mixed linear models with bootstrapping). We will not perform subgroup analyses. Additionally, analyses of variance and *χ*
^2^ tests will be employed to examine potential differences in sociodemographic and clinical data among various subgroups, such as dropouts, participants who completed the intervention, and those who benefitted from the intervention.

Exploratory analyses, including regression analyses, will be conducted to investigate the relationship between usage behavior and clinical outcomes, considering all assessments including in-treatment assessments. Secondary endpoints will include the examination of time to dropout using the Kaplan-Meier estimate and Cox proportional hazards regression. Here, a standard proportional hazards model—using the *coxph* function from the *survival* package in R—will be applied. Differences in time to dropout between the treatment and the control group will be assessed. Also, the baseline values of the relevant psychometric measures of depression and mental distress (CESD-R, PHQ-4, DT), self-efficacy (GSES), quality of life (WHOQOL), and eating behavior (EDI-2, EDE-Q8), as well as sociodemographic and medical characteristics (gender, SES, BMI), will be entered into the regression model to explore potential determinants of dropout. In case of large deviations from constant hazards (which will be tested using the *cox.zph* function from the abovementioned package), we will explore underlying reasons and might, for instance, further assess non-linear effects or models with stratification according to certain covariates.

To ensure safety assessment, separate tabulations and line listings of adverse events and severe adverse events will be generated for comprehensive analysis.

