**Methods:**

The trial incorporates four distinct measurement time points: the baseline assessment, the post-treatment assessment, and 1- and 3-month follow-up assessments. Furthermore, we implemented in-treatment assessments for both groups. Participants will be randomized into two groups (LightMood intervention vs TAU). The aim is to include 128 participants (64 per group) in the study. Inclusion criteria are patients who are obese, at least 18 years old, with a private Internet access, and with adequate digital literacy and show depression symptoms (PHQ ≥ 10). Exclusion criteria are weekly outpatient individual psychotherapy, obesity surgery within the last year or planned within the next 7 months, no private Internet access, and the prescription of a new psychotropic drug within the last 2 weeks. The primary outcome is the post-assessment reduction in depression symptoms. Secondary outcomes will include the improvement in self-efficacy, quality of life, mindfulness, reduction in eating disorder symptoms, and body mass index (BMI). Furthermore, we expect a positive development of depression symptoms throughout the different time points (T1, T2, and T3) in patients with obesity.

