**Secondary outcomes**					
GSES	x		x	x	
WHOQOL	x		x	x	
FFA	x		x	x	
EDI-2	x		x	x	
EDE-Q8	x		x	x	
CSQ-I			x		x
SUS			x		x
Usage behavior		x			
UTAUT	x				
PHQ-4	x	x	x	x	x
DT	x	x	x	x	x
BMI	x		x	x	
Sociodemographics, medical characteristics	x				

*CESD-R* Center of Epidemiologic Studies Depression Scale-Revised, *GSES* General Self-Efficacy Scale, *WHOQOL* World Health Organization Quality of Life, *FFA* Freiburger Fragebogen zur Achtsamkeit,*EDI-2* Eating Disorder Inventory Bulimia subscales, *EDE-Q8* Eating Disorder Examination Questionnaire, measuring Eating Disorder specific Symptoms, *CSQ-I* Client Satisfaction Questionnaire Internet-based, *SUS* System Usability Scale, *UTAUT* Unified Theory of Acceptance and Use of Technology questionnaire, *PHQ-4* Patient Health Questionnaire-4, *DT* distress thermometer, *BMI* body mass index

A participant who has decided to quit during the intervention counts as a dropout (no login for 6 weeks is considered as a dropout). Patient who drop out of the study will be asked to complete a dropout assessment. The participant who decides to drop out will be contacted (if written permission was given) by study personnel so that the drop-out assessment can be sent to the participant.

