#### Control intervention

In the proposed RCT, the intervention group will be compared with a control group. The intervention will be compared to the usual care the participants receive in conventional healthcare in Germany. Hence, there is no restriction regarding access to therapeutic and/or medical services during the trial. Besides that, the participants in the control condition do not receive any additional treatment. The control group participants will not have access to any content of the LightMood intervention. Instead, they will receive every week notifications via mail for the in-treatment assessment, which will be conducted online by the participants.

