*Course/development of depression symptoms and distress*: Depression and anxiety symptoms: The Patient Health Questionnaire-4 [36] in its validated German version is used to measure depression and anxiety symptoms. The PHQ-4 is a proven short questionnaire consisting of four items: two items on depression symptoms (PHQ-2) and two items on generalized anxiety symptoms (Generalized Anxiety Disorder Scale-2 (GAD-2)). Responses are rated on a 4-point Likert scale for all four items. The PHQ-4 will be applied to all patients throughout the study.
*Distress:* Distress and its progression, measured with the Distress Thermometer [37], will be analyzed in all patients throughout the study. The DT is an efficient and convenient validated measurement tool for assessing exposure. It is an established and rapid screening tool for stress, acting as a visual thermometer on a scale of 0 (no stress) to 10 (more extreme stress).

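### The imputation for the primary analysis names only sex, age and baseline scores, although in-treatment and follow-up scores that predict a missing T1 CESD-R better are collected; if symptom-driven dropout differs by arm, the T1 contrast is biased

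*Protocol article*

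**What the plan says.** Statistical methods in the protocol article defines the primary analysis: "we will employ an analysis of covariance (ANCOVA) with the outcome measured at T1", adjusted for the T0 value. It continues: "The primary analysis will be conducted on the intention-to-treat population, with missing data imputed in cases of dropout". The imputation uses the SPSS module, "employing “monotone missing pattern” and incorporating complete data for sex, age, and baseline measurements of primary and secondary outcomes", with 3000 imputations and a seed rule. The method is therefore fixed in this document and not deferred.

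Other sections show what else is collected:

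- Abstract, Methods: "Furthermore, we implemented in-treatment assessments for both groups".
- Control intervention, on TAU participants: "they will receive every week notifications via mail for the in-treatment assessment".
- Outcomes, on depression and anxiety symptoms: "The PHQ-4 will be applied to all patients throughout the study". On distress, the DT "will be analyzed in all patients throughout the study".
- Study design, Table 1: PHQ-4 and DT are marked as in-treatment measures. CESD-R is marked at baseline, end of treatment, follow-up (T2 and T3) and the drop-out assessment.
- Study design, below Table 1: "Patient who drop out of the study will be asked to complete a dropout assessment".

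Statistical methods names in-treatment data only for exploratory regressions of clinical outcomes on usage. Nothing brings them, or the T2/T3 scores, into the imputation.

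**The concern.** Imputation from baseline variables is valid if, given those variables and arm, missingness at T1 is unrelated to the T1 score. Symptom course after randomization is an obvious way for that to fail: people who feel worse, or who have already improved, may stop. The arms also disengage from different things. LightMood participants must finish one module to unlock the next, whereas TAU participants receive only questionnaires, and all participants know their allocation. Under Statistical methods the sponsor itself plans to compare time to dropout between arms.

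If the link between symptoms and dropout differs by arm, observed T1 scores are a distorted sample of each arm to a different degree. Imputing from baseline carries that distortion into the treatment contrast. At stake is the estimate for the primary hypothesis, in a trial that plans for 30% dropout.

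**Working it through.** **Inputs from the protocol (Sample size calculation):** d = 0.5 at T1, correlation r = 0.5 between repeated measures, 30% dropout from T0 to T3, 49 per arm effective and 64 per arm randomized.

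**Check that these are read on the right scale.** ANCOVA power with 49 per arm: standardized effect 0.5/√(1 − 0.5²) = 0.577, 95 degrees of freedom, two-sided 0.05 (assumed, as alpha is not stated). The result is 80.75% against the stated 80.34%. The standard error of the contrast is √(0.75 × 2/49) = 0.175 SD, or √(0.75 × 2/64) = 0.153 SD with all 64 per arm observed.

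**Assumptions not in the documents:** a late in-treatment score M with correlation 0.5 to baseline and 0.7 to T1; a treatment effect of 0.35 SD on M; logistic dropout on M with the slopes below (log-odds per SD), set to the stated missing rate in each arm. A positive slope means that people with worse scores leave. Arm is in every imputation model shown.

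**Size by hand.** Given baseline, T1 regresses on M with slope (0.7 − 0.5 × 0.5)/(1 − 0.5²) = 0.45/0.75 = 0.6. With slope 1 in LightMood and 0 in TAU, LightMood dropouts exceed completers on baseline-adjusted M by about 0.63 SD (from simulation). Bias ≈ 0.30 × 0.6 × 0.63 = 0.11 SD.

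**Large-sample simulation (1,000,000 participants per scenario), true benefit 0.50 SD:**

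| Slope LightMood / TAU | Missing at T1 | Baseline + arm | With M added |
|---|---|---|---|
| 1 / 0 | 30% | 0.62 | 0.50 |
| 1 / 0 | 20% | 0.58 | 0.50 |
| 1 / 0 | 15% | 0.56 | 0.50 |
| 1 / 0.5 | 30% | 0.55 | 0.50 |
| 2 / 0 | 30% | 0.68 | 0.50 |
| −1 / 0 | 30% | 0.38 | 0.50 |
| 1 / 1 | 30% | 0.50 | 0.50 |

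At 30% missing the bias thus runs from 0.55 − 0.50 = 0.05 to 0.68 − 0.50 = 0.18 SD, or 0.05/0.175 = 0.3 to 0.18/0.175 = 1.0 standard errors. It can go either way. With no true effect, slopes 1/0 and 2/0 give a spurious benefit of 0.12 and 0.18 SD, and slope 1/1 gives none.

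**If the driving score is not observed.** For slope 1/0 at 30% missing, replace M by an earlier score that correlates 0.7 with it. The estimate moves from 0.616 to 0.568, so (0.616 − 0.568)/(0.616 − 0.500) = 41% of the bias is removed. With correlation 0.5 it moves to 0.59, about 20%.

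**At trial size** (64 per arm, 30% missing, 1,500 trials per scenario, two-sided 0.05, in-treatment/T1 correlation 0.6 to 0.8, M observed for everyone). With slope 1/0 and no true effect, baseline + arm imputation rejects in 8 to 11% of trials; with M added, in about 5%. If values are missing completely at random, neither model is biased, and at correlations of 0.7 to 0.8 power rises from about 76% to 80–84% when M is added.

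**The case against.** The case on the other side is substantial, and several parts of it stand.

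- **The bias is conditional.** Multiple imputation from baseline covariates is a recognized missing-at-random analysis. The material biases all come from slopes that differ between arms, and no section supports particular slopes. With equal slopes and equal dropout rates the bias vanishes. If one rule holds in both arms, so that rates differ slightly because of the treatment effect, it is at most about 0.06 SD and absent under no effect. This stands. For the same reason, opposite-signed slopes, which give larger figures, are left out of the range above.
- **30% is an upper bound.** It covers T0 to T3, including loss to follow-up. This stands, and the 15% and 20% rows show the effect.
- **The monotone method.** A reader might infer that it wrongly assumes nobody who misses T1 answers T2. The primary analysis does not support that. Randomization follows a completed baseline, so with complete predictors T1 CESD-R is the only incomplete variable, and that pattern is monotone by construction. The method becomes unsuitable only once in-treatment or T2/T3 scores enter.
- **Full recovery.** A reader might infer that adding in-treatment scores removes the bias altogether. Six weeks without login counts as dropout, so many dropouts may have no late score, and the correction is then partial.
- **Drop-out CESD-R.** It looks like the natural predictor, but it is collected from dropouts, while T1 is observed mainly in completers. Few people will have both, so their relation can hardly be estimated.
- **The list does not say that nothing else is used.** True, but it specifies baseline measurements, and no other sentence adds a post-baseline score. The omission is the plain reading.

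What remains is that better predictors of the missing primary outcome are collected and the stated model does not name them.

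**Conclusion.** The concern holds as a conditional weakness in a stated method. The plan contains no contradiction or wrong figure here. With symptom-driven dropout that differs by arm, the T1 contrast is off by about 0.05 to 0.18 SD at 30% missing, and by less at lower missingness; if both arms share the same slope it is off by about zero. This rests on the protocol's r = 0.5 and on assumed values for the in-treatment/T1 correlation (0.7) and the dropout slopes. The documents do not show that such dropout will occur. They show only a setting in which it is plausible: unblinded participants, and an app compared with usual care. In-treatment scores reduce the bias, fully or by roughly 40% depending on which scores dropouts leave behind, and can add precision even if there is no bias. T2/T3 scores help only for people who miss T1 and return, and their benefit was not simulated. The change is worth making before the analysis, because it concerns the primary outcome and uses data already collected.

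**What to change.** Revise the imputation sentence in Statistical methods so that the predictors are:

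- arm, which the present list does not name;
- sex, age and the baseline scores already listed;
- a small summary of in-treatment PHQ-4 and DT, for example the last available value of each;
- CESD-R at T2 and T3.

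Replace the monotone method by fully conditional specification, because in-treatment and T2/T3 scores will be missing in non-monotone patterns. Do not enter the drop-out CESD-R as an ordinary predictor of T1; keep it for a sensitivity analysis of how far dropouts depart from the imputed values.

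The cost is revised wording and a somewhat larger imputation model to check at n = 128, which is why the in-treatment summary should stay short. The 3000 imputations may have to be reduced if the larger model runs slowly.

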#### Sample size calculation

The calculation of the sample size was performed using the R-package “Superpower” [38]. Our primary hypothesis is that the intervention will be superior in terms of reducing depression symptoms compared to TAU (control group) at T1. To assess the efficacy of the intervention, we will conduct an ANCOVA analysis with the primary outcome variable at T1 as the dependent variable, the group variable (intervention vs. control group) as a between-subject factor, and the individual baseline levels at T0 as a covariate. Subsequently, a mixed ANOVA analysis with the respective measurements (T0–T3) as a within-subject factor and the group variable as a between-subject factor will be used to explore the intervention’s effect at follow-up.

For the sample size calculation, we selected a preferred test power of 1 − *ß* = 0.80. We anticipate a moderate effect size of *d* = 0.5 for the baseline-adjusted comparison between the intervention and control group at T1. Based on previous studies, we expect the correlation between repeated measures to be *r* = 0.5 [39].

According to the power analyses, a total effective sample size of *n* = 98 (49 participants per group) will provide a statistical power of 80.34 for the ANCOVA analysis mentioned above. With the same number of participants, we achieve a power of 95.8 for the mixed ANOVA analysis mentioned earlier, assuming a conservative assumption that the sole difference between the intervention and control group occurs at T1.

Considering a dropout rate of 30% from T0 to T3, based on existing literature on eHealth trials [40], we estimate that 128 participants (64 per group) will be required. This dropout rate includes loss to follow-up.

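### The listed imputation predictors for the primary analysis omit randomised group; run as listed, the imputation shrinks the treatment effect by roughly the share of T1 scores that are missing

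*Protocol article*

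**What the plan says.** All of this is in the Statistical methods section of the protocol article unless noted.

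- Analysis model: an ANCOVA of the T1 outcome "using the between-subject factor of the group (intervention vs. control) and the participants’ baseline values (T0) as a covariate".
- Population and missing data: "The primary analysis will be conducted on the intention-to-treat population, with missing data imputed in cases of dropout".
- Imputation predictors: "incorporating complete data for sex, age, and baseline measurements of primary and secondary outcomes". Group is not among them.
- Other settings: the software module and a monotone pattern are named, and "The imputation process will be executed with 3000 imputations, using the analysis date as the seed".
- Sample size calculation section: "We anticipate a moderate effect size of *d* = 0.5 for the baseline-adjusted comparison between the intervention and control group at T1", and "we expect the correlation between repeated measures to be *r* = 0.5". With 49 per group this "will provide a statistical power of 80.34 for the ANCOVA analysis mentioned above". The number randomised is 128 (64 per group), allowing for 30% dropout between T0 and T3. No separate figure is given for T1.

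**The concern.** The primary test asks whether group affects T1 CESD-R after adjustment for baseline. An imputation model that contains baseline variables but not group assumes that, among those with missing T1 data, the two arms have the same expected score given baseline. The imputed cases then carry no treatment difference, whatever the observed cases show. The analysis model contains a term that the imputation model sets to zero.

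The other listed predictors cannot make up for this, because randomisation makes them independent of arm. A large number of imputations does not help either: it only reduces the simulation noise around the attenuated value. At stake are the size of the reported primary effect and the power of the only confirmatory test.

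**Working it through.** **Inputs.** From the Sample size calculation section: 64 per arm randomised, 49 per arm effective, d = 0.5, r = 0.5. Allocation is 1:1 (randomization section). Assumed, because not stated: two-sided alpha 0.05, and T1 missingness of 15% to 30%. Within that range, 23.4% = 1 − 98/128 is the loss that would leave the planned effective 98.

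**Step 1: reproduce the plan's power.** The ANCOVA residual SD is √(1 − r²) = √0.75 = 0.866. The noncentrality is (0.5/0.866) × √(49/2) = 0.577 × 4.950 = 2.86, on 98 − 3 = 95 df. The noncentral t gives 80.75%, against the stated 80.34. The inputs are therefore read as the plan meant them.

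**Step 2: expected attenuation.** Let a fraction m of T1 scores be missing at random in each arm, and let the true adjusted difference be d. With group left out, every imputed score is centred, given baseline, on the pooled mean of the observed cases, which lies d/2 from each arm's own mean.
- Intervention arm: (1 − m)(−d) + m(−d/2)
- Control arm: (1 − m)(0) + m(−d/2)
- Difference: −(1 − m)d

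With d = 0.5 the expected estimate is 0.85 × 0.5 = 0.425 at 15% missing, 0.400 at 20%, 0.383 at 23.4% and 0.350 at 30%.

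**Step 3: simulation.** 3000 trials per scenario, 64 per arm, T1 missing completely at random (a special case of missing at random). Proper normal-regression imputation used 30 draws and Rubin's rules with small-sample df, followed by the planned ANCOVA. Baseline CESD-R was the only covariate. Monte Carlo error on power is at most about √(0.46 × 0.54/3000) = 0.9 points.

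| T1 missing | Estimate, no arm | Power, no arm | Estimate, with arm | Power, with arm |
|---|---|---|---|---|
| 15% | 0.43 | 74% | 0.50 | 84% |
| 20% | 0.40 | 67% | 0.51 | 83% |
| 23.4% | 0.38 | 58% | 0.49 | 79% |
| 30% | 0.35 | 46% | 0.50 | 74% |
| 40% intervention, 20% control | 0.34 | 42% | 0.49 | 73% |

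The estimates agree with Step 2. A separate run with 1500 trials and 60 imputations per trial gave 0.35 and 46% without arm, and 0.50 and 75% with arm, at 30% missing.

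**Step 4: behaviour under the null.** At 30% missing the rejection rate is 0.7% without arm and 5.3% with arm. In the 1500-trial run (d = 0.5, 30% missing, no arm) the mean pooled standard error was 0.181, while the estimates had an empirical SD of only 0.130. The test divides by a standard error about 0.181/0.130 = 1.4 times too large, which is why it rejects too rarely.

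**The case against.** **The list may not be complete.** The sentence does not say that only these variables are used, and it does not name the variables to be imputed. Group is known for everyone and appears in the ANCOVA a few lines earlier, so its absence could be shorthand. A statistical analysis plan is mentioned as available on request and is not shown here. This stands as a limit: a reader might infer that arm is definitely excluded, but the text shows only that it is not named. The point survives because the article goes beyond a general reference to imputation. It sets the software, the pattern, the number of imputations, the seed rule and a predictor list, and someone following it literally would leave arm out. The blinding of the primary-analysis statisticians makes that reading more plausible.

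**The 30% belongs to a different time point.** It runs from T0 to T3 and includes loss to follow-up; the primary outcome is at T1, three months before T3. This stands, and 30% is treated as the upper end of an assumed range. A reader might infer that an effect of the planned size would probably be missed. That holds only near 30% missing (or with unequal loss such as 40% and 20%). From 15% to 23.4% missing, power without arm is 74% to 58%, so detection remains more likely than not.

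**Dropouts may lose the benefit.** If so, pooled draws could lie nearer the truth than draws that use arm. A reader might infer that the reported effect would be wrong in every case; the bias is relative to the missing-at-random effect. The article, however, does not present the pooled draws as a deliberate assumption about dropouts.

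**The error is conservative.** This also stands. The oversized standard error even keeps the 95% interval's coverage of 0.50 close to nominal (93.8% at 30% missing), but the point estimate and the power still suffer.

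**Conclusion.** The concern holds as a conditional statement about the rule as written. The predictor list omits randomised group, and no within-arm imputation is described. Followed literally, the primary effect is multiplied by about one minus the T1 missing fraction: a loss of some 15% to 30% of the effect and of about 10 to 28 power points (84 − 74 at 15% missing; 74 − 46 at 30%).

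This rests on the list being the full model, on T1 data missing at random, on the assumed missingness range and alpha, and on the plan's own d and r. It does not establish that the analysis will in fact be run without arm, or that the trial would probably fail. It is more than an omitted detail, because the rule as stated gives a biased primary estimate and an over-conservative test, and it is easily corrected before analysis.

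**What to change.** State that randomised group is a predictor in the imputation model, or that imputation is done separately by arm, for T1 CESD-R and every other imputed outcome. Keep sex, age and the baseline scores as listed. A coded arm label is enough and keeps the statistician blinded. If group is already in the planned model, one clause saying so settles the point.

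If pooled-arm draws are meant as a cautious assumption about dropouts, keep them as a labelled sensitivity analysis with that rationale written down, not as the primary method.

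The cost is one clause in the plan and one extra variable in the imputation call, with no new data or visits and no unblinding.

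### The T0–T3 mixed ANOVAs for follow-up and secondary outcomes carry no stated population or missing-data rule; unless imputation is extended to them, they use only participants with all four visits

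*Protocol article*

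**What the plan says.** Under Statistical methods, the primary analysis is an ANCOVA of the CESD-R at T1 with the T0 score as covariate. For that analysis the population and the missing-data rule are given: "The primary analysis will be conducted on the intention-to-treat population, with missing data imputed in cases of dropout". The imputation is described as "incorporating complete data for sex, age, and baseline measurements of primary and secondary outcomes".

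The next paragraph turns to sustained effect: "Subsequent mixed ANOVAs will be conducted with a between-subject factor representing group membership (intervention vs. control"). Time enters these models over all four visits, baseline included. For secondary outcomes: "Further mixed ANOVAs will be used to assess the impact of the intervention on the secondary outcome measures". No population and no missing-data rule is attached to either. The type of mixed ANOVA is shown by the sentence "Corrections, such as Huynh-Feldt or Greenhouse-Geisser, will be implemented if the assumption of sphericity is violated in the mixed ANOVA", which belongs to the classical repeated-measures method. Generalized estimating equations and robust mixed linear models are named as replacements, but the trigger is a departure from normality or homoscedasticity, not missing visits. One further sentence says that additional clinical endpoints will be handled in a comparable way, without mentioning imputation or intention-to-treat.

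Under Sample size calculation: "Considering a dropout rate of 30% from T0 to T3, based on existing literature on eHealth trials". Beneath Table 1: "Patient who drop out of the study will be asked to complete a dropout assessment". In that table the drop-out column has CESD-R, PHQ-4, DT, CSQ-I and SUS, but not GSES, WHOQOL, FFA, EDI-2, EDE-Q8 or BMI.

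**The concern.** A classical mixed ANOVA needs a value at every level of the within-subject factor. A participant who misses T3 therefore leaves the whole analysis, including an observed T1 and T2. The protocol names this method for the very span over which it forecasts 30% loss, and it states a remedy for missing data only for another analysis.

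At stake are the secondary superiority hypotheses and the expectation of sustained gains at T2 and T3 (Objectives and hypotheses). Participants are not blinded and only one arm has a programme to abandon, so dropout that differs by arm is plausible. The loss of precision does not depend on that.

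**Working it through.** **Inputs.** From Sample size calculation: 128 randomised (64 per group), 30% lost from T0 to T3, effective n = 98 (49 per group), d = 0.5, r = 0.5, group difference at T1 only for the mixed ANOVA. Assumed, because the article does not give them: two-sided alpha 0.05, equal correlation between all visits, outcome SD = 1, and the split of the loss before and after T1.

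**1. The plan's own figures.** ANCOVA, 49 per group, residual SD = √(1 − 0.5²) = √0.75: power 80.8% by noncentral t, against the stated 80.34%. This reproduces. For the group-by-time interaction, λ = (n/2)·Σc²/(1 − r), where c is the pattern of differences (0, 0.5, 0, 0) centred on its mean, so Σc² = 0.1875, with df = 3 and 3(2n − 2). At n = 49, λ = 24.5 × 0.1875/0.5 = 9.19 and power is 71.5%, against the stated 95.8%. This does not reproduce from the stated inputs; it is a separate matter and is not relied on here.

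**2. Complete cases.** 128 × 0.70 = 89.6, about 90 (45 per group). This is below the 98 of the power statement, because 98 × 1.30 = 127.4 gives 128, while 98/0.70 = 140.

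**3. Interaction power by number of complete cases.**

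| Per group | λ | Power |
|---|---|---|
| 45 | 8.44 | 67.3% |
| 49 | 9.19 | 71.5% |
| 64 | 12.00 | 83.6% |

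The last row assumes complete data on everyone. No method reaches it with 30% lost, so it is an upper bound and not the power of the proposed model.

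**4. Precision of the T1 contrast under random loss.** A change score has variance 2(1 − r) = 1, so with 45 complete cases per group SE = √(2/45) = 0.211. If half the loss (15%) comes before T1, 64 × 0.85 = 54.4 per group have T1, and with baseline adjustment SE = √(2 × 0.75/54.4) = 0.166. Two things contribute to the gain. Baseline adjustment alone on the complete cases gives √(1.5/45) = 0.183; recovering the discarded T1 values brings it to 0.166. If all loss came before T1 the figure stays at 0.183; if all came after, it is √(1.5/64) = 0.153.

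**5. Bias under assumed dropout rules.** Negative values favour LightMood on the CESD-R.

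- No true effect; 15% lost at random before T1, then 17.6% of the rest; in the LightMood arm only, the log-odds of leaving rise by 0.8 to 1.2 per SD of poorer change at T1. Simulated bias in the completers' T1 contrast is about -0.14 to -0.19 SD, and the interaction test rejects in about 7% to 11% of trials instead of 5%. An estimate from all observed T1 data stays unbiased.
- True effect -0.50 at T1–T3; 30% lost per arm, depending on the T1 score. The completers' T1 contrast is -0.50 under random loss, -0.50 with the same rule in both arms, -0.63 if worse-scoring LightMood participants leave, and -0.37 if better-scoring ones leave (control loss random in the last two).

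The later visits are less affected. Under the first rule dropout follows T1 − T0, and cov(T3 − T0, T1 − T0) = 0.5 − 0.5 − 0.5 + 1 = 0.5, against a variance of 1 for T1 − T0, so the T3 bias is half the T1 bias. Under the second rule the T3 contrast stayed at about -0.50.

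**The case against.** The protocol never declares a completers analysis and never confines imputation to the primary endpoint. The sentence on additional clinical endpoints follows the ANCOVA, the imputation and the mixed ANOVA, and may be meant to cover all three. The imputation already draws on baseline values of secondary outcomes, and a monotone pattern suits sequential dropout over T1–T3. The article condenses a fuller plan and mentions a separate statistical analysis plan. The follow-up mixed ANOVA is described in the sample size section as exploring the effect.

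Much of this stands. A reader might infer that imputation is ruled out for these analyses and that dropouts cannot be scored. The document does not support that: it is silent rather than restrictive, and dropouts who return the drop-out assessment will have a CESD-R score, though not at a scheduled visit. A reader might also infer that the results will be inflated in favour of LightMood. That needs a particular arm-specific mechanism; other mechanisms give no bias in the T1 contrast or the reverse. Nor is the gap between 83.6% and 67.3% the price of choosing mixed ANOVA, since the first figure is for complete data. The likelihood estimate is unbiased in the simulations because every dropout rule there depends on observed values, which is not evidence of robustness beyond that.

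What does not fall away is the choice of method. This is more than detail left to another document: the article picks a method that cannot use incomplete participants, forecasts that nearly a third will be incomplete, and makes its more tolerant alternatives conditional on something else.

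**Conclusion.** The concern holds in a conditional form. As written, the CESD-R follow-up analysis and the secondary clinical analyses rest on about 90 of 128 participants unless imputation is extended to them, which the text does not clearly say. The certain cost is precision: a T1 standard error of about 0.21 SD against 0.17 for an analysis of all observed T1 data with baseline adjustment (0.15 to 0.18 over the possible splits of the loss), given r = 0.5 and 30% loss. Bias is possible but its size and sign rest on an assumed dropout mechanism. The imputed intention-to-treat analysis of the primary outcome at T1 is not touched.

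**What to change.** Analyse the CESD-R follow-up and each secondary clinical outcome with a likelihood-based linear mixed model for repeated measures, using all observed visits of all randomised participants, with group, time, group-by-time and baseline score, and report the group difference with confidence interval at each visit. Do not exclude by rule those without a post-baseline value, since that would sit badly with intention-to-treat; entering baseline as a response with a common mean across arms keeps them in.

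Alternatively, extend the planned multiple imputation to T1–T3 and the secondary outcomes. The imputation model should then include group and the observed earlier visits, which the listed predictors (sex, age, baseline measurements) do not.

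Either way, state that intention-to-treat applies to these analyses, and keep any complete-case mixed ANOVA as a labelled sensitivity analysis.

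The cost is wording and a little more analysis work. No new data or participants are needed, and mixed linear models are already planned for the mediation analysis. The downside is reliance on data being missing at random given what was observed. With the mixed model as main method, the sphericity corrections are needed only for the sensitivity analysis.
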